### **13.2. Sample Size and Feasibility**

It is postulated that approximately 25% of patients having the CT of the abdomen and pelvis alone will receive either palliative care (~10%) or EFRT (~15%). The use PET-CT in addition to CT of the abdomen and pelvis would be considered valuable if the proportion of patients treated with either palliative care or EFRT increased to 45% (20% and 25% respectively). These estimates are derived using the estimates available from the previous smaller studies performed on the older PET scanners. Further, a 20% absolute difference was felt to be a clinically important difference and is slightly more conservative than the 50% relative change in treatment rate observed in the OCOG trial of PET in early lung cancer. Based on these considerations, a trial with 288 patients (192 PET-CT, 96 CT abdomen and pelvis) will have over 90% power to detect a difference of this magnitude using the Fisher's exact test ( $\alpha=0.05$ , two-sided).

The 2:1 randomization for this trial allows us to gain additional understanding of the potential effect of FDG PET-CT plus CT of the abdomen and pelvis to CT of the abdomen and pelvis alone, which is currently the standard of care in patients with locally advanced cancer of the cervix. Using this unbalanced allocation will increase the number of patients who receive FDG PET-CT and could potentially help with recruitment. We feel this is ethical as preliminary data indicate the use of PET-CT may be better than CT abdomen and pelvis alone and it is unlikely that PET-CT will be detrimental to the individual patient. (Although unlikely to be detrimental, it is unclear that there is a benefit and even if a benefit exists, whether it is sufficient to warrant extensive use of PET-CT, hence the rationale for the study).

With a traditional 1:1 randomization, 128 patients per arm (256 in total) would be required. By using the 2:1 randomization scheme, 32 additional patients will need to be recruited to a total of 288 subjects. However, at the end of the study, 64 more patients will have undergone PET-CT (consequently, 32 fewer patients will have CT abdomen and pelvis alone) compared to 1:1 randomization, while maintaining  $\alpha=0.05$  and 90% power for a two-sided test. By gaining additional information on 64 more patients with PET-CT, we will have better estimates of the true change in management rate due to PET-CT, and of EFS and OS resulting from the use of PET-CT. Further, these additional patients will give us more

information to investigate the effect of PET SUV on EFS in this patient population, which is an important scientific question. Thus, it is felt the small increase in total sample size is warranted.

In Ontario for the fiscal period 2003-2004, there were 513 women who presented with cervical cancer: 220 did not receive surgery and 186 had a radiation oncology consult and treatment planning. These data have not changed significantly since then. Thus, a conservative estimate of recruitment is approximately 120 subjects per year. Based on these considerations, and an anticipated 6 month startup period, recruitment will be complete in approximately 2.5 years from study commencement. The Investigators involved in this trial include gynecologic oncologists and radiation oncologists who have a strong track record of recruitment to clinical trials.

Steps will be put in place to minimize losses to follow-up. Clinical trials staff will pursue rebooking any appointments that are not kept. Losses to follow-up in trials are known to be lower than in standard care. In OCOG's PET trials, the loss to follow-up rate is very low. There are a certain small number of patients who do not undergo PET due to comorbid conditions or other outside circumstances.

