## 13. STATISTICAL CONSIDERATIONS

### 13.1. Statistical Analysis

The primary outcome is treatment delivered. Exact tests will be used to investigate a difference in the proportion of patients receiving standard pelvic chemo-radiotherapy of curative intent, more extensive chemo-radiotherapy of curative intent or therapy with palliative or non-curative intent both unadjusted (e.g. exact  $\chi^2$  test) and after adjusting for the stratification factors (e.g. logistic regression). A secondary analysis will explore the specific treatments delivered (e.g. brachytherapy dose and volume, parametrial boost doses, external radiation dose and volume, fractions, overall treatment duration, radiotherapy technique – IMRT versus conventional radiotherapy, chemotherapy dose and duration) using descriptive statistics.

The longer term question concerns the subsequent EFS and OS of patients following EFRT. If, as anticipated, the PET-CT strategy is able to generate a cohort of patients who have para-aortic nodal disease that is curable by EFRT, then the 5-year EFS and OS of patients following surgery would be expected to be higher for patients in the CT abdomen and pelvis + whole body PET-CT group *versus* the CT abdomen and pelvis group. EFS and OS will be estimated and plotted for each arm separately using Kaplan-Meier methods; the treatment arms will be compared using Cox proportional hazards regression models.

The prognostic ability of PET SUV of cervical cancer will be investigated as a risk factor for EFS and OS using Cox proportional hazards regression models amongst those patients

undergoing PET-CT only. Economic and Quality of Life analyses are described in Appendices IV, V and IX.

Some missing data is expected for economic outcomes and will be assumed to be missing at random. Missing data will be left as missing for other outcomes (e.g. baseline information) and descriptive statistics will be used to report the number of missing results. Missing data is not expected to occur for the primary outcome except in cases where patients withdraw from the study or rapidly deteriorate. In this case, the planned treatment will be used in lieu of treatment delivered.

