All tests will be two-sided and based on an intent-to-treat analysis. A p-value of 0.05 or less will be considered statistically significant. In addition, 95% confidence intervals will be constructed for outcomes of interest. All data analysis will be performed using the latest versions of SAS (Cary, NC) and using StatXact (Boston, MA).

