### **13.6. Planned Interim Analysis**

One planned interim efficacy analysis will be performed after 50% of patients have been accrued. The Haybittle-Peto approach will be used, such that if the proportion of patients receiving standard pelvic chemo-radiation following CT abdomen and pelvis + PET-CT is significantly less (one-sided  $\alpha=0.001$ ) than the proportion of patients receiving standard pelvic chemo-radiation following CT abdomen and pelvis alone, then the Data Safety Monitoring Board (DSMB) will be expected to recommend to the Steering Committee that the trial should be discontinued early. In addition to the interim analysis based on efficacy, the DSMB will review accumulating safety data annually, starting approximately twelve months after study commencement. The Steering Committee will make the final decision about study continuation based on these recommendations.

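### The power of over 90% in Section 13.2 belongs to a two-category Fisher test; the three-category exact test that Section 13.1 most naturally describes has about 86%

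*Protocol*

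**What the plan says.** **Outcome.** Sections 2.2 and 12.1 classify treatment delivered into three categories: (1) standard pelvic chemo-radiotherapy of curative intent, (2) more extensive curative chemo-radiotherapy such as EFRT, (3) palliative or non-curative therapy.

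**Sizing.** Section 13.2 merges categories 2 and 3. It assumes 25% in the CT arm (palliative about 10%, EFRT about 15%). PET-CT would be worthwhile if "the proportion of patients treated with either palliative care or EFRT increased to 45% (20% and 25% respectively"). It adds that "a 20% absolute difference was felt to be a clinically important difference", and concludes that the 288-patient trial "will have over 90% power to detect a difference of this magnitude using the Fisher's exact test" at a two-sided level of 0.05. The later paragraph of 13.2 on 1:1 allocation repeats 90% power and gives 128 per arm as the 1:1 equivalent.

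**Interim.** Section 13.6 stops the trial if "the proportion of patients receiving standard pelvic chemo-radiation following CT abdomen and pelvis + PET-CT is significantly less" than in the CT arm, at a one-sided level of 0.001. This is again category 1 against the rest.

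**Final analysis.** Section 13.1 says: "Exact tests will be used to investigate a difference in the proportion of patients receiving standard pelvic chemo-radiotherapy of curative intent, more extensive chemo-radiotherapy", and the sentence goes on to name the third category. An exact chi-square test is the example given for the unadjusted analysis, and logistic regression for the analysis adjusted for stratification factors. The significance rule is "All tests will be two-sided and based on an intent-to-treat analysis. A p-value of 0.05 or less will be considered statistically significant". No sentence combines categories 2 and 3 for this test.

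**The concern.** A power statement describes one test of one hypothesis. Sizing and interim use a comparison of two proportions (one degree of freedom). The final test, as 13.1 reads, is a comparison of three-category distributions (two degrees of freedom). Two things follow if that reading is what is carried out.

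First, the extra degree of freedom costs power under the alternative the protocol itself postulates, so the stated figure does not apply to the primary test.

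Second, the two tests respond to different departures from the null. The two-category test responds only to movement into or out of standard treatment, which is the quantity 13.2 and 13.6 rely on. The three-category test also responds to movement between EFRT and palliative care. A significant primary result would therefore not by itself show the effect on which the trial was justified.

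**Working it through.** **Inputs (Section 13.2 unless noted)**
- CT arm, n = 96: standard/EFRT/palliative = 0.75/0.15/0.10.
- PET-CT arm, n = 192: 0.55/0.25/0.20.
- Two-sided level 0.05 (13.1 and 13.2). Allocation 2:1 (Section 6.2).

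**Step 1: reproduce the plan's figure (two categories)**

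With p1 = 0.25, p2 = 0.45, r = 2 and pooled p = (0.25 + 2 × 0.45)/3 = 0.3833, the usual formula for the CT arm is

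n = [1.960·√(1.5 × 0.3833 × 0.6167) + 1.2816·√(0.1875 + 0.2475/2)]² / 0.20² = (1.167 + 0.715)² / 0.04 ≈ 88.6, rounded up to 89.

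The continuity correction gives (88.6/4)·[1 + √(1 + 6/(88.6 × 2 × 0.20))]² ≈ 96, hence 96 + 192 = 288. The same calculation at 1:1 gives 118 per arm uncorrected and 128 corrected. Both of the protocol's sample sizes reproduce.

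The exact power of the two-sided Fisher test is the sum of Bin(x1; 96, 0.25) × Bin(x2; 192, 0.45) over all tables with Fisher p ≤ 0.05:
- 192/96: **91.5%**
- 128/128: **90.3%**

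So the claim in 13.2 is right for the two-category test.

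**Step 2: same alternative, three categories**

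The pooled proportions are (0.75 + 2 × 0.55)/3 = 0.6167, (0.15 + 2 × 0.25)/3 = 0.2167 and (0.10 + 2 × 0.20)/3 = 0.1667. The noncentrality is (n1·n2/N) × Σ(difference²/pooled), with n1·n2/N = 96 × 192/288 = 64:

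λ = 64 × (0.04/0.6167 + 0.01/0.2167 + 0.01/0.1667) = 64 × 0.1710 = 10.95.

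- Noncentral chi-square on 2 df: power 85.1%.
- Exact conditional tests, by simulation with 20,000 and 30,000 trials: 86.2% to 86.5%, for both the exact Pearson chi-square and the Fisher-Freeman-Halton test. The simulation standard error is about √(0.86 × 0.14/30,000) = 0.2 percentage points.

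Type II error therefore goes from 8.5% to about 14%. At 128/128 the exact three-category power is about 87%. To reach 90% at 2:1, the three-category test needs about 324 patients by exact simulation (216/108: 90.2%) or 333 by the asymptotic formula (222/111: 90.0%).

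**Step 3: standard treatment unchanged at 75% in both arms**

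The protocol gives no such scenario, so the PET-CT splits below are assumptions chosen to show a range. The CT arm stays at 75/15/10, with n = 192/96.

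| PET-CT arm (standard/EFRT/palliative) | λ | Three-category rejection, asymptotic | Three-category rejection, exact (8,000 simulations) | Two-category Fisher rejection |
|---|---|---|---|---|
| 75/10/15 | 2.57 | 28.0% | about 28% | 4.2% |
| 75/20/5 | 3.27 | 34.8% | 35–36% | 4.2% |
| 75/5/20 | 11.52 | 86.9% | about 87% | 4.2% |

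For example, the first row is λ = 64 × (0.0025/0.1167 + 0.0025/0.1333) = 2.57. The two-category figure is the same in every row because only the mix within categories 2 and 3 changes.

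**The case against.** The best reply is that 13.1 does not fix a three-category test. It speaks of exact tests in the plural, and puts the chi-square and the logistic regression forward only as examples. Logistic regression is most often binary. The rest of the protocol leans the same way: 13.2, 13.6 and the cost-effectiveness ratio in Appendix IX all use a single probability of leaving standard treatment. A two-category test may have been intended, and an analysis plan could say so.

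That much stands: the three-category test is the natural reading, not the only one. But the power figure, the primary comparison and the stopping rule are all stated in Section 13, and 13.1 lists three categories without combining any. The mismatch lies inside the protocol, and readers cannot tell which test the stated power protects.

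Four stronger readings are tempting, and the documents do not support them:
- **That the power figure is miscalculated.** It reproduces; it belongs to a different test.
- **That design, interim and final analysis all test different hypotheses.** Design and interim share one contrast. Only the final analysis, as written, departs from it.
- **That naming logistic regression is incompatible with three categories.** Multinomial and ordinal logistic models exist. The protocol simply does not say which kind is meant.
- **That a significant result driven by the EFRT/palliative mix would be a false positive.** Section 2.2 sets out to compare treatments delivered across three classes, so such a shift is a real difference under the stated objective. The 87% case is also the extreme of the assumed splits: EFRT falls from 15% to 5% while palliative care doubles. Section 13.2 expects both to rise.

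**Conclusion.** The point holds as a mismatch between the powered contrast and the primary analysis as written. Under the protocol's own category split, the three-category exact test has about 86% power (85.1% asymptotically), against 91.5% for the two-category Fisher test behind the stated figure. The shortfall is about 5 percentage points and depends on reading 13.1 as a comparison across three categories. The no-change scenarios, with about 28%, 35% and 87% rejection against about 4%, rest on assumed splits. They show that the two tests answer different questions; they do not predict what the trial will find.

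This should be fixed, but it does not threaten the trial's validity. Each test, specified in advance, controls type I error, and 86% is still reasonable power. What is missing is a primary hypothesis that matches the sample size statement.

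**What to change.** **Preferred.** In 13.1, name the two-sided Fisher exact test of category 1 against categories 2 and 3 combined as the primary test. Specify the adjusted analysis as a binary logistic model on that same outcome, and report the three-category comparison as supportive. Sections 13.1, 13.2 and 13.6 then agree, and 288 patients keep 91.5% power. The cost is one paragraph, with no change in sample size or data collection.

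**Alternative.** Keep the three-category exact test as primary, which follows the wording of 2.2 more closely. Then restate the power in 13.2 as about 86% for 192/96 (and about 87% for the 128-per-arm comparison), say in 13.1 that the adjusted model is multinomial, and note in 13.6 that the interim contrast is narrower than the final one. This too is only wording. Restoring 90% power instead would need about 324 to 333 patients, which is 36 to 45 more. At the protocol's 120 per year that is 36/120 = 0.30 to 45/120 = 0.38 of a year of extra accrual.

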### **13.3. Analysis Sets**

All patients who are randomized will be included in the Full Analysis set. All patients who complete the baseline QoL and at least one follow-up QoL questionnaire will be included in the QoL Analysis set.

Analysis of the treatment delivered, EFS and OS will be based on the Full Analysis set with patients included in groups according to their randomized allocation (i.e. intention-to-treat principle). A secondary analysis of treatment delivered, EFS and OS will be performed on the protocol evaluable analysis set, defined as the subset of patients in the Full Analysis set excluding patients with disease which has spread to distant organs. Analysis of QoL and economic outcomes will be based on the QoL Analysis set. Investigation of the prognostic ability of PET SUVs will be based on the patients who underwent PET-CT.

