| Belhocine                                       | 22 | 0.56        | 0.98        | 0.72                 | 0.97        |                           |             |
| Pooled                                          |    | 0.79        | 0.99        |                      |             |                           |             |

The pooled sensitivity for  $^{18}\text{F}$ FDG PET for detection of para-aortic nodes was 0.84 and the pooled specificity was 0.95. There was insufficient information on conventional imaging with MR and CT. These authors also identified four studies on the accuracy of PET for pelvic nodes. Two studies used lymphadenectomy as the gold standard and two used clinical follow-up. The pooled sensitivity was 0.79 and pooled specificity was 0.99. Two studies each had data on CT and MRI. Although the numbers are small, there is a suggestion that the accuracy of PET is better than that for CT or MRI. More recent studies have supported the notion that PET is more accurate than CT or MRI in identifying disease.

There have been other case series that reported on staging of cervix cancer with PET imaging. In summary, the available evidence suggests that PET is more accurate than conventional imaging. However, the number of patients studied is relatively small, the studies are old (2005 or earlier) and uncontrolled and none of the studies used modern PET-CT.

Thus, PET-CT imaging can upstage patients, with the potential to improve treatment for patients with more extensive disease. An example of this might be a patient with normal-sized pelvic nodes on CT scan who would be treated more effectively with para-aortic RT if

PET-CT demonstrated positive nodes. Conversely, if PET-CT detected metastatic disease outside the pelvis and para-aortic nodes not found by conventional imaging (e.g. in one study 8% of patients had supraclavicular nodal metastases detected by PET), these patients would be spared chemo-RT and receive palliative care.

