#### **4.2.1. Inclusion Criteria**

For inclusion in this study, patients must fulfill all of the following criteria:

1. Women with newly diagnosed histologically confirmed FIGO Stage IB-IVA carcinoma of the cervix (see **Appendix I**), including squamous, adenosquamous or adenocarcinoma. Women not suitable for surgery due to comorbidities (medical or other conditions) are also considered eligible;
2.  $\geq 18$  years of age;
3. Being considered for treatment with curative intent using concurrent chemotherapy and pelvic RT.

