| Stage IV   | The carcinoma has extended beyond the true pelvis or involves (biopsy proven) the mucosa of the bladder or rectum. A bullous edema, as such, does not permit a case to be allotted to Stage IV.                                                                                                                                                                                                                                                                                                                                     |
| Stage IVA  | Spread of the growth to adjacent organs. Invades mucosa of bladder or rectum and/or extends beyond true pelvis                                                                                                                                                                                                                                                                                                                                                                                                                      |
| Stage IVB  | Spread to distant organs                                                                                                                                                                                                                                                                                                                                                                                                                                                                                                            |

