**5. Field of View**

The same field of view should be used for both CT and PET imaging. Image from the base of the skull down to the mid thigh.

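### The secondary protocol evaluable set excludes patients with distant spread without saying when or how it is found; applied to post-randomization imaging, it biases EFS and OS towards PET-CT and treatment delivered against it

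*Protocol*

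**What the plan says.** Section 13.3 of the protocol has two layers. The main one is sound: "Analysis of the treatment delivered, EFS and OS will be based on the Full Analysis set", with patients grouped as randomized. Then "A secondary analysis of treatment delivered, EFS and OS will be performed on the protocol evaluable analysis set", which is defined as "the subset of patients in the Full Analysis set excluding patients with disease which has spread to distant organs". No date, imaging test or confirmation rule is attached to that exclusion.

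Four other places bear on who would be excluded:

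- **Entry.** Section 4.2.1 admits "newly diagnosed histologically confirmed FIGO Stage IB-IVA carcinoma of the cervix". In Appendix I the words "Spread to distant organs" define stage IVB, which is not eligible.
- **PET-CT arm.** Appendix VI, item 5, instructs: "Image from the base of the skull down to the mid thigh".
- **CT arm.** Section 7.2 gives CT of the abdomen and pelvis. Under Section 6, a contrast CT done within 6 weeks before randomization is not repeated, so some CT-arm patients have no protocol staging scan after randomization. Chest film or chest CT precedes randomization in both arms (Section 5).
- **Expectation.** Section 1.5 describes what follows "if PET-CT detected metastatic disease outside the pelvis and para-aortic nodes not found by conventional imaging": palliative care in place of chemo-radiotherapy. Section 13.2 plans for palliative treatment of about 10% with CT and 20% with PET-CT.

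**The concern.** An analysis set should not depend on the result of the randomized intervention. Here a PET-CT patient whose distant disease is seen on the scan leaves the set. A CT-arm patient with the same disease, unseen, stays in and brings a poor prognosis with her. The PET-CT subset then survives better even if PET-CT changes nothing for anyone, which is stage migration.

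Treatment delivered moves the other way. Palliative therapy is category 3 of the primary outcome (Section 12.1), and the exclusion removes more of it from the PET-CT arm.

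At stake is a prespecified survival comparison that could show a benefit where none exists. Section 13.1 already anticipates higher 5-year EFS and OS with PET-CT, so such a result would look like confirmation. Section 12.1 does discuss a detection bias, but only for liver metastases and prior CT, and not for this set.

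**Working it through.** **1. The plan's own figure.** Section 13.2 states over 90% power for 25% versus 45% non-standard treatment with 96 CT and 192 PET-CT patients (Fisher's exact test, two-sided 0.05). Exact enumeration gives 91.5%. The figure reproduces, and it refers to all randomized patients.

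**2. Spurious survival difference with no true effect.** Let *D* be the true proportion with distant spread, equal in both arms. PET-CT finds all of it; CT finds a proportion *c* of all patients. Five-year OS is *m* with spread and *g* without.

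- Full Analysis set, each arm: *Dm* + (1 − *D*)*g*, so the difference is 0.
- Evaluable, PET-CT: *g*.
- Evaluable, CT: [(1 − *D*)*g* + (*D* − *c*)*m*] / (1 − *c*).
- Spurious gain: (*D* − *c*)(*g* − *m*) / (1 − *c*).

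Inputs: *m* = 17.2% (stage IVB, Table 1). The values of *g* (55–65%), *D* and *c* are assumptions. The 20% and 10% in the last three rows borrow the palliative planning rates. HR is approximated by ln(*g*) / ln(CT value).

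| *D* | *c* | *g* | CT, evaluable | Gain | HR |
|---|---|---|---|---|---|
| 4% | 2% | 60% | (0.96×0.60 + 0.02×0.172)/0.98 = 59.1% | 0.9 points | 0.97 |
| 8% | 4% | 60% | (0.92×0.60 + 0.04×0.172)/0.96 = 58.2% | 1.8 points | 0.94 |
| 20% | 10% | 55% | (0.80×0.55 + 0.10×0.172)/0.90 = 50.8% | 4.2 points | 0.88 |
| 20% | 10% | 60% | (0.80×0.60 + 0.10×0.172)/0.90 = 55.2% | 4.8 points | 0.86 |
| 20% | 10% | 65% | (0.80×0.65 + 0.10×0.172)/0.90 = 59.7% | 5.3 points | 0.84 |

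The gain is positive whenever PET-CT finds more spread than CT and spread worsens survival. It grows if CT finds less than half. The protocol gives no EFS rates, so EFS is not quantified; the same argument sets its direction.

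**3. Treatment delivered.** Let *p* and *c* be the proportions excluded from the PET-CT and CT arms, and suppose every excluded patient would have been treated palliatively. Non-standard treatment becomes (0.45 − *p*)/(1 − *p*) versus (0.25 − *c*)/(1 − *c*).

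- *p* = 20%, *c* = 10% (planning rates): 0.25/0.80 = 31.3% versus 0.15/0.90 = 16.7%. The contrast is 14.6 points instead of 20. About 154 and 86 patients remain, and exact power is about 69%.
- *p* = 10%, *c* = 5%: 0.35/0.90 = 38.9% versus 0.20/0.95 = 21.1%, or 17.8 points.
- *p* = 4%, *c* = 2%: 0.41/0.96 = 42.7% versus 0.23/0.98 = 23.5%, or 19.2 points.
- *p* = 20%, *c* = 5% (more lopsided): 31.3% versus 21.1%, or 10.2 points.

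The shrinkage comes from the unequal exclusion. Equal exclusion of 10% in both arms would give 0.20/0.90 = 22.2 points. The contrast falls when 0.55*p*/(1 − *p*) exceeds 0.75*c*/(1 − *c*), as in every unequal case above.

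**The case against.** **The set is secondary.** Treatment delivered, EFS and OS are all analysed first on the Full Analysis set by allocation, Section 13.1 makes tests intention-to-treat, and neither the sample size nor the interim rule uses this set. This stands. A reader might infer that the trial's primary conclusion is compromised; the protocol does not support that.

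**The text does not say the spread is found after randomization.** This also stands as a point of wording. Appendix I says clinical stage must not be changed because of later findings, so the exclusion could mean only ineligible stage IVB entrants, and some imaging does precede randomization. But on that reading the set removes almost nobody and serves no purpose. Any reading under which it does real work draws mainly on post-randomization findings. A reader might go further and take the undated wording to cover later distant relapse, which would condition on the EFS event itself; nothing in the protocol shows that this is meant.

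**The larger figures equate distant-organ spread with palliative treatment.** This stands. Table 5 routes supraclavicular and mediastinal nodes to palliation alongside organ disease, the 8% cited in Section 1.5 is nodal, and Section 12.1 calls liver metastases rare. Applying stage IVB survival to disease visible only on PET is a further assumption. A reader might take 4 to 5 points as the expected bias; it is the result at high assumed prevalence, and a narrow reading of distant organs gives about 1 to 2 points. The sign does not change.

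**Conclusion.** The exclusion is undefined and, in the only form in which it matters, depends on the randomized imaging. With no true effect, the evaluable set would show a spurious 5-year OS gain for PET-CT of about 0.9 points at 4% prevalence, 1.8 at 8% and 4.8 at 20% (4.2 to 5.3 for OS of 55–65% without spread). These figures assume equal true disease in the two arms, CT finding half of what PET-CT finds, and 17.2% survival with spread.

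Treatment delivered is biased in the opposite direction: from 20 to about 14.6 points at the planning rates if palliative treatment stands in for distant spread, less if exclusions are proportionately fewer, and more if they are more lopsided. It would be wrong to say that the set favours PET-CT on every outcome.

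This should be fixed. It does not threaten the intention-to-treat analysis.

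**What to change.** Either drop the protocol evaluable set as a between-arm comparison of treatment delivered, EFS and OS, or define it only on findings recorded before randomization in both arms: baseline FIGO stage, chest film or chest CT, and any abdomen and pelvis CT already done by then. Report patients whose distant spread is found after randomization descriptively, by arm, with the test that found it.

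The cost is a change of wording in Section 13.3, with no new data or patients. A PET-blinded re-read of CT scans is not needed; the protocol provides for none, and it would be extra work. The downside of the restricted definition is that the set will differ little from the Full Analysis set, which is also a reason simply to drop it.
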